### Core Methods and Measures

The following general aspects of a common study protocol were considered essential features of the ATOP study design. Each of these is described in more detail below.1. Contextual Description of Treatment Settings.• Original and/or existing ethnographic description.• Interviews with program managers, staff, and healers.2. Observational design with mixed methods• Baseline, discharge and periodic post-discharge measurement of treatment outcomes with validated, quantitative measures, with minimum of one-year post-discharge follow-up.• Scheduled semi-structured interviews with study participants for qualitative analysis.

At the present time, the Takiwasi Center remains the first and only active ATOP study site. The ATOP-Takiwasi study was initiated in January 2016 and this paper reports the protocol used in data collection and analysis for the mixed-methods program evaluation, including post-treatment follow-up. Preliminary results have been published on select mental health outcomes achieved during treatment (Giovannetti et al., 2020) and on samples of Takiwasi patients assessed with selected measures prior to implementation of the full protocol reported on here (O’Shaughnessy, 2017; Berlowitz et al., 2019). As described below, the research team is now poized to report on the first cohort of patients followed for a full 12 months after discharge. Negotiations continue in Mexico in order to meet importation and other regulatory requirements for implementing the ATOP protocol at Nierika Center.

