*Quantitative analytics—Patients* The quantitative analysis team is composed of three team members, aided by an external native Spanish-speaking volunteer. Among the formal team members, one is a native Spanish speaker and two speak Spanish at an intermediate level. The data preparation and analysis will proceed through six steps: 1) preparation of a unified, person-level Excel data file that includes all baseline and subsequent quantitative data points as well as abstracted information from patient files; 2) descriptive analysis of the characteristics of the study sample with frequency distributions and cross-tabulations (see Supplementary Table S1); 3) descriptive analysis of patients’ treatment participation and perceived importance of Takiwasi treatment activities (see Supplementary Table S2); 4) visualization of trends over time across the range plethora outcome measures (See Supplementary Table S3). Importantly, statistical significance testing is not performed on any observed changes over time in these multiple outcomes so as not to violate the principles on which the subsequent stage of multivariate modeling is based (i.e., mitigating increased odds of Type 1 error across multiple, non-theory driven comparisons) (Kuchibhotla et al., 2020); 5) a team-based, measures minimization process so as to reduce the number of predictor and outcome variables based on previous research and a priori conceptual modeling of hypothesized relationships. For example, of the many measures of substance use and problem indicators, one or possibly two primary substance use outcomes measures will be identified, and as well many potential predictor and moderator variables associated with mental health, treatment motivation, treatment participation and ratings of program experience. Finally, 6) Preparation of DAGs (Directed Acyclic Graphs) to conceptually model the hypothesized relationship between predictor and moderating variables and outcome. These DAGs then serve as the basis for multivariate regression modeling (Herman and Robins, 2020). Regression analyses will start with less complex, three to five variable DAGS and build from there based on variance explained through addition of predictors and moderators (Hernan and Robins, 2020) with due consideration for statistical power. See Supplementary Figure S1 for an example of a hypothesized and relatively complex DAG.

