The research protocol, described above in detail, is poized to make a significant contribution toward each of four study goals. Our first goal is to contribute to an understanding of ayahuasca-assisted treatment for substance use disorders. Our mixed methods approach within a longitudinal cohort design, situated in the context of complexity-based evaluation, will be critical to identifying key elements of set and setting that are most closely associated with treatment outcomes. To this end, the major strengths of the protocol include: the use of multiple, validated measures of predictors, potential moderators, and outcomes, which are assessed at multiple time points from program entry through 24 months post-discharge; multiple measures of program participation and satisfaction with services; and state-of-the-art statistical testing methods that will minimize risks of Type I error that can arise through multiple, non-theory-based significance testing. The comparative approach to addressing research questions via complementary quantitative and qualitative analytics is similar conceptually to that employed by Thomas et al. 2013 and Argento et al. (2019) in their study of ayahuasca-assisted treatment for substance use disorders in Canada, but now advantaged with a more extensive baseline assessment of patient characteristics, a larger sample size and longer follow-up period. As the current research progresses toward its first analysis and reporting on one-year follow data, it will prove to be the most rigorous and comprehensive study to date focused exclusively on ayahuasca-assisted treatment for substance use disorders.

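### The primary substance use outcomes are chosen after all outcome trends have been plotted, so mitigation of Type I error is not assured for change from baseline to 12 months

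*Protocol article*

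**What the plan says.** All references are to the protocol article.

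- **Order of work** (Analysis Plan, quantitative analytics for patients). Step 1 assembles one file with baseline and all later data. Step 4 is the "visualization of trends over time across the range plethora outcome measures". Step 5 is "a team-based, measures minimization process so as to reduce the number of predictor and outcome variables". At that step "one or possibly two primary substance use outcomes measures will be identified"; the criterion given for the reduction is that it is "based on previous research and a priori conceptual modeling of hypothesized relationships". Step 6 draws the DAGs.
- **Safeguard at step 4.** The plan says that "statistical significance testing is not performed on any observed changes over time in these multiple outcomes", with the aim of "mitigating increased odds of Type 1 error across multiple, non-theory driven comparisons".
- **After step 6.** Post-discharge outcomes relative to baseline are analysed with a generalized linear mixed effects model. The DAGs are to be drawn before any model is fitted, and estimates from every fitted model are to be reported.
- **Claim in the Discussion.** Among the major strengths are "state-of-the-art statistical testing methods that will minimize risks of Type I error" of the kind that comes from many tests without a theoretical basis.
- **Status** (Study Recruitment and Measuring Treatment Exposure). By December 2020, 48 of the 60 participants scheduled for the one-year follow-up had completed it. The article names no primary outcome and still puts the choice in the future.

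**The concern.** A primary outcome protects against multiplicity only if it is fixed without knowledge of the results. Here the team would look at the course of every outcome and then decide which one or two are primary. Leaving out significance tests at step 4 does not remove the problem: picking the curve that moved most is the same selection as picking the smallest p-value, without the p-value being written down.

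The first key quantitative question is what outcomes are achieved at 12 months after discharge. The cohort has no control group, so change from baseline carries that answer. If the choice were influenced by the plots, p-values, intervals and effect sizes for that change could be too favourable, while the Discussion would present them as protected.

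**Working it through.** **No figure to reproduce.** The article states no alpha, power or effect size for these analyses. The calculation only shows how much could be at stake.

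**Inputs**
- From the article: n = 48 with 12-month data, and the order of steps 4, 5 and 6.
- Assumed: k candidate outcomes; common correlation r between their change scores; one-sided alpha 2.5% (two-sided 5%); no true change in any outcome; the most favourable outcome is always chosen. The article does not count the candidates. Table 1 lists two substance use instruments, the Addiction Severity Index and the GAIN substance use grid, each of which can give several scores. Small k therefore has to be shown beside larger k.

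**Method.** For each outcome j, t_j = mean change ÷ (SD ÷ √48). The outcome with the largest t_j is chosen and called positive if t_j exceeds the 97.5th percentile of t with 47 df, which is 2.01. There were 20,000 simulated trials per setting.

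**Bound by hand.** For independent outcomes the rate is 1 − 0.975^k. For k = 2 this is 1 − 0.975² = 4.9%, and for k = 3 it is 1 − 0.975³ = 7.3%. Positive correlation lowers these values.

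**Worst-case result for change from baseline**

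| k | r | One-sided false-positive rate (nominal 2.5%) |
|---|---|---|
| 2 | 0.5 | 4.7% |
| 3 | 0.5 | 6.2% |
| 8 | 0.5 | 12.8% |
| 12 | 0.3 | 20.6% |

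For k = 8 and r = 0.5 the two-sided rate is about 25% against 5% if the largest change in either direction is picked. The chosen outcome then shows a spurious mean improvement of about 0.15 SD; for k = 2–3 it is 0.06–0.09 SD. If the choice ignores the plots, the rate stays at 2.5%.

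**Second key question, predictors of outcome.** In simulations with k = 3, 5 and 10 and r from 0 to 0.7, the outcome with the largest improvement was picked and an unrelated predictor was then tested on it at two-sided 5%. The rejection rate was 4.8–5.2%. Choosing the outcome by its pooled trend does not by itself inflate these tests.

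**Do the stated safeguards close the gap?**
- *A priori basis for step 5:* this is the intended criterion, but it is applied after the plots, and nothing shows that the choice is independent of them.
- *DAGs before model fitting:* they come before the models but after the plots.
- *Reporting of all fitted models:* an outcome dropped at step 5 may never have a model, so the selection would not show.

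**The case against.** The strongest case is that the article gives a proper criterion for step 5, namely earlier research and prior conceptual modelling, and nowhere says that trends guide the choice. If that criterion is followed, there is no inflation. The article also promises only to mitigate or minimise Type I error, not to control it at a stated level, and testing one or two outcomes instead of many does reduce the risk. It describes itself as an observational cohort that cannot support strong causal statements. A fuller plan, not shown, may name the outcomes.

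Most of this stands, and it limits the point. Three stronger readings are tempting but are not supported:

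- *That there is no protection at all, or that the results will be biased.* The stated basis, the prior DAGs and the full reporting are partial protection. The article fails to rule out a choice influenced by the trends; it does not describe one.
- *That the predictor analyses are inflated too.* The check above shows that this selection alone does not do so. The Analysis Plan ties its Type I error remark to the stage of multivariate modelling.
- *That earlier publication has already revealed the outcomes.* The article says "Preliminary results have been published on select mental health outcomes achieved during treatment". Mental health scores during treatment do not show substance use trends at 12 months.

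What the objection does not remove is the printed order itself. A fuller plan that named the outcomes beforehand would be at odds with the sequence in this article.

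**Conclusion.** The point holds in a limited form. As sequenced, the primary substance use outcomes and the DAGs are settled only after all trends have been plotted, and no safeguard makes the choice independent of the plots. Mitigation of Type I error is therefore not assured for change from baseline to 12 months; a reader may not conclude that it is absent.

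The size is an upper bound, not an expected effect: about 5–6% for k = 2–3 and about 13% for k = 8 at r = 0.5, up to about 21% for k = 12 at r = 0.3, against a one-sided 2.5%. It rests on assumed k, r and alpha and on always taking the most favourable outcome. The matter is worth settling before the 12-month analysis, because independence of the choice cannot be restored once the choosers have seen the trends.

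**What to change.** 1. Move the reduction of measures and the DAGs (steps 5 and 6) ahead of the trend plots (step 4). Alternatively, have the outcomes chosen by people who have not seen follow-up outcome data.
2. Record in a dated memo the one or two primary substance use outcomes and the 12-month time point. If there are two, state how alpha is shared: two independent tests at 5% each give 1 − 0.95² = 9.75%, and at 2.5% each 1 − 0.975² = 4.94%.
3. Label all other outcomes descriptive.
4. If trends have already been viewed, disclose it, call the change-from-baseline results exploratory, and qualify the Type I error statement in the Discussion.

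The cost is a reordering of steps and a short memo. What is lost is the freedom to choose outcomes after seeing them.

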Post-discharge outcomes relative to baseline will be analyzed with a generalized linear mixed effects model. Random intercepts (and random slopes where necessary) will be included to account for correlation between observations within study participants. The regression models will also include (potentially time-varying) baseline and within-treatment covariates (e.g., treatment motivation, baseline addiction severity, and number of hours engaged in non-ayahuasca treatment activities such as psychotherapy, group integration, ergotherapy). Statistical inference will proceed in a manner consistent with the DAGs constructed before any models are fit. The relevant parameter and variance estimates associated with all models that are fit will be reported.

*Qualitative analytics—Patients* The qualitative team is composed of four researchers, two of which are native Spanish-speakers, and the other two speak Spanish at an expert level. Qualitative analysis will employ a grounded theory approach (Miles and Huberman, 1994; Strauss and Corbin, 1994), in which the team creates codebooks based on themes that emerge from the interview data with inpatients. Grounded theory approaches work best with relatively open-ended questions and narratives which allow for deep analysis and emergence of key themes, which ultimately become integral to building a case-specific theory about outcomes related to set and setting at Takiwasi. In line with this approach, the original guiding research questions may be modified in an iterative process according to significant themes that emerge in the data.

The team selected a cloud-based qualitative data analysis program (www.dedoose.com) through which they can remotely cross-code data and conduct collaborative analyses. Analysis will focus on several themes guided by the specific research questions, including recovery capital, expectations and perceptions of treatment, spirituality, religiosity, and social influences, among others.

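### Enlarging the regression models by variance explained is a data-driven rule that conflicts with inference from DAGs drawn before fitting

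*Protocol article*

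**What the plan says.** The rule is in the Protocol article, Analysis Plan, quantitative analytics for patients.

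- Step 5 is a team-based exercise to "reduce the number of predictor and outcome variables based on previous research and a priori conceptual modeling of hypothesized relationships". Its illustrative example mentions "many potential predictor and moderator variables associated with mental health, treatment motivation, treatment participation and ratings of program experience". The number left after the reduction is not given.
- Step 6 draws DAGs and says: "These DAGs then serve as the basis for multivariate regression modeling". It continues: "Regression analyses will start with less complex, three to five variable DAGS", and from there the models are to "build from there based on variance explained through addition of predictors and moderators", "with due consideration for statistical power".
- The next paragraph, on the mixed models, says: "Statistical inference will proceed in a manner consistent with the DAGs constructed before any models are fit". It also promises: "The relevant parameter and variance estimates associated with all models that are fit will be reported".

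Two other places bear on the rule. Step 4 withholds significance tests of change over time so that the modelling stage is protected from Type I error through comparisons not driven by theory. The Discussion, under the first study goal, repeats that protection as a strength. The second key quantitative question asks which factors are independently associated with 12-month outcomes. Its examples mix baseline variables (motivation, severity) with discharge status.

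**The concern.** A DAG determines which covariates belong in a model from assumed causal structure, before the data are consulted. How much variance a covariate explains plays no part in that decision. A rule that adds terms because they explain variance makes the decision after fitting, from the outcome data.

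The two criteria can point in opposite directions. Variables close to the outcome in time, such as discharge status or treatment participation, tend to explain most variance. They may also lie on the path from a baseline factor to the outcome. A confounder may explain little variance and still be needed. A model built on variance explained can therefore have the wrong adjustment set, an optimistic R², and p-values and intervals that ignore the search. The answer to the second key question, and the claimed protection against Type I error, both depend on this.

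**Working it through.** **1. The passages side by side.** Models rest on DAGs (step 6). Inference follows DAGs fixed before any fit (mixed-model paragraph). Enlargement follows variance explained (step 6). The first two statements agree. The third needs a quantity that exists only after fitting. Read plainly, a model enlarged by that criterion was not fixed in advance.

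**2. Sample size.** The recruitment section gives 128 intakes and 42 exits before any ayahuasca, so 128 − 42 = 86 baseline interviews. At 12 months it gives 48 of 60 scheduled: 48/60 = 80%, as stated. The 48 is the count at 17 December 2020. Follow-up continues to at least 2023.

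**3. Wrong adjustment set.** Take a baseline factor X, a discharge status M = 0.6X + noise, and an outcome Y = 0.6M + noise (noise SD 0.8 in each). The true total effect of X is 0.6 × 0.6 = 0.36. Over 5,000 simulated samples of 48:
- X alone: mean estimate 0.36, mean R² 0.14.
- X with M added: mean estimate for X 0.00, mean R² 0.38.

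A variance-explained rule would prefer the second model, which removes the total effect of X.

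**4. Selection from noise.** Assumptions not in the article: alpha 0.05, the candidate counts, independent normal candidates, a single linear outcome with no true predictor, and a fixed number of terms added in order of variance explained, then tested naively. Two comparators separate selection from other causes:
- k prespecified independent tests: P(at least one p<0.05) = 1 − 0.95^k. For k = 5, 10, 15, 20 this is 22.6%, 40.1%, 53.7%, 64.2%.
- m noise terms fixed in advance: expected R² = m/(n − 1). At n = 48 this is 3/47 = 0.06 and 5/47 = 0.11.

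| Candidates | Terms added | Selected: at least one p<0.05 | Prespecified tests | Difference (points) | Mean R², selected | Expected R², fixed in advance |
|---|---|---|---|---|---|---|
| 5 | 3 | 26% | 23% | 3 | 0.10 | 0.06 |
| 10 | 3 | 49% | 40% | 9 | 0.16 | 0.06 |
| 15 | 5 | 72% | 54% | 18 | 0.25 | 0.11 |
| 20 | 5 | 84% | 64% | 20 | 0.29 | 0.11 |

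Repeat runs moved the selected percentages by about 2 points.

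**5. Sensitivity to the entry rule.** At n = 48 with 5, 10 and 20 noise candidates, the chance that at least one enters is 23%, 40% and 65% if entry needs p<0.05. It is 85%, 98% and 99.9% if entry needs only a rise in adjusted R².

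**6. Sensitivity to n.** With entry at p<0.05, the rates at n = 69 (0.8 × 86 = 68.8) and n = 86 are nearly unchanged: about 23%, 40% and 63–66%. With a fixed number of added terms, n = 86 gives about 44–47%, 64% and 76% for 10, 15 and 20 candidates, against 49%, 72% and 84% at n = 48. Noise R² falls more clearly: with 20 candidates and adjusted-R² entry it is 0.35 at n = 48, 0.24 at 69 and 0.19 at 86.

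**The case against.** The best case for the plan is that step 6 enlarges the DAG, and that the mixed-model paragraph governs: the team steps through progressively larger DAGs, all drawn beforehand, and tracks variance explained along the way. The article refers to an example of a relatively complex DAG in its supplement. On this reading nothing is selected. A variable that affects only the outcome may also be added for precision without breaching a DAG, so the two criteria are not always incompatible. This reading is possible, but the sentence makes variance explained the ground for enlarging, so it still needs rewording.

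The plan also has safeguards. Step 5 reduces candidates on prior research. With 5 survivors and 3 additions, selection adds only about 3 points. Power is to be considered, which bears on model size and not on how terms are chosen. All fitted models are to be reported, which limits selective reporting but does not correct intervals or p-values after selection.

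Including discharge status is not an error in itself, because the second key question is about association and names it. The Limitations also concede that strong causal statements are not possible. The harm arises when discharge status enters a model that is then read for a baseline factor's effect.

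Finally, the simulation uses one linear outcome, whereas the plan uses a mixed model with repeated measures. Its global null is also pessimistic for predictors chosen on theory.

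**Conclusion.** The point holds as a conflict in the plan's stated rules. As written, step 6 enlarges models by a data-driven criterion resembling forward selection. That does not fit with inference from DAGs fixed before fitting or with the stated Type I error aim.

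The firmer harms are wrong adjustment sets and optimistic R². Under the assumptions above, mean noise R² is 0.10 to 0.29, against 0.06 to 0.11 for the same number of terms fixed in advance. The excess in false significance due to selection is about 3 to 20 points; the rest of the 26% to 84% is ordinary multiplicity. These sizes depend on candidate counts and an entry rule that the article does not give.

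A reader might infer three stronger things that the document does not support:
- **That the plan prescribes forward stepwise regression.** It names no algorithm or threshold.
- **That false predictors are certain.** They are a probability, and it depends on the assumed settings.
- **That the sample of 48 is the cause.** It is an interim count. False-entry rates under a fixed p-value threshold barely change with n; a small n mainly inflates R².

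**What to change.** In step 6, delete the words that make variance explained the basis for enlarging models. State instead that:

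- for each exposure of interest, the model's covariates are the adjustment set implied by its DAG, and are fixed before that model is fitted;
- variance explained is reported as description only;
- any model enlarged after fitting is labelled exploratory.

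If the intention was to step through larger DAGs drawn in advance, say so and list them.

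The cost is a wording change and no new data. Fewer predictors will be declared and reported R² will be lower. The change removes the search but not the multiplicity: at an assumed alpha of 0.05, five prespecified exposures still carry a 23% chance of at least one false positive, and ten carry 40%. Acknowledge this when the results are interpreted.
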